
# 2. STUDY OBJECTIVES

## 2.1 Primary Aim 1

Enumerate and characterize camps where young men at risk for HIV acquisition and transmission socialize in four wards of Dar es Salaam.

## 2.2 Primary Aim 2

To determine whether men in camps randomized to receive a microfinance and health leadership intervention have a lower prevalence of sexually transmitted infections (NG, TV, CT), and report perpetrating less physical or sexual violence against female sexual partners as compared to men in camps not randomized to receive the intervention.

## 2.3 Secondary Aim

To determine whether men in camps randomized to receive a microfinance and health leadership intervention report less risky and greater protective behaviors related to HIV acquisition including: gender equity, alcohol and drug use, sexual relations and risk behavior, uptake of HIV counseling and testing; unprotected sexual intercourse; consistent condom use; delay of sexual debut; number of sexual partners, and sexual concurrency.

In the event that program effects are identified, a secondary objective is to assess the degree to which the following mediate the impact of the multi-level intervention on STI and gender-based violence: Hope, Future Orientation, Social Cohesion, Social Support, Collective Efficacy, Emotional Distress, and Sexual Networks

# 3. STUDY DESIGN

## 3.1 STUDY SCHEDULE

This study, from planning through data analysis, is scheduled to last 5 years. The intervention component of the study will last 2 years. A timeline for the project is presented below.

| Activity | Year1 | | | | Year 2 | | | | Year 3 | | | | Year 4 | | | | Year 5 | | | |
| --- | --- | --- | --- | --- | --- | --- | --- | --- | --- | --- | --- | --- | --- | --- | --- | --- | --- | --- | --- | --- |
|  | 1 | 2 | 3 | 4 | 1 | 2 | 3 | 4 | 1 | 2 | 3 | 4 | 1 | 2 | 3 | 4 | 1 | 2 | 3 | 4 |
| Planning and obtaining approvals |  |  |  |  |  |  |  |  |  |  |  |  |  |  |  |  |  |  |  |  |
| Developing protocols |  |  |  |  |  |  |  |  |  |  |  |  |  |  |  |  |  |  |  |  |
| Staff recruitment and training |  |  |  |  |  |  |  |  |  |  |  |  |  |  |  |  |  |  |  |  |
| Identification and enumeration of camps |  |  |  |  |  |  |  |  |  |  |  |  |  |  |  |  |  |  |  |  |
| Screening and enrollment |  |  |  |  |  |  |  |  |  |  |  |  |  |  |  |  |  |  |  |  |
| Baseline assessment |  |  |  |  |  |  |  |  |  |  |  |  |  |  |  |  |  |  |  |  |
| Randomization |  |  |  |  |  |  |  |  |  |  |  |  |  |  |  |  |  |  |  |  |
| Intervention |  |  |  |  |  |  |  |  |  |  |  |  |  |  |  |  |  |  |  |  |
| Qualitative cohort interviews |  |  |  |  |  |  |  |  |  |  |  |  |  |  |  |  |  |  |  |  |
| Follow-up assessment |  |  |  |  |  |  |  |  |  |  |  |  |  |  |  |  |  |  |  |  |
| Data cleaning and analysis |  |  |  |  |  |  |  |  |  |  |  |  |  |  |  |  |  |  |  |  |
| Dissemination |  |  |  |  |  |  |  |  |  |  |  |  |  |  |  |  |  |  |  |  |

## 3.2 Trial Design

### 3.2.1 Overview

This is a cluster randomized controlled trial to assess the efficacy of an intervention designed to reduce HIV risk and gender-based violence among young men who socialize in camps in Dar es Salaam, Tanzania. Sixty camps in four economically disadvantaged wards within Dar es Salaam will be randomized to receive either two years of a combined microfinance and health leadership intervention or a control condition. We will conduct quantitative assessments at baseline, 12 months and 30 months, and three qualitative assessments through the life of the study.

### 3.2.2 First Primary Aim

To accomplish the first primary aim to enumerate and characterize camps within four wards in Dar es Salaam, a PLACE (Priorities for Local AIDS Control Efforts) assessment will be conducted. PLACE is venue-based sampling methodology that was developed to identify venues where individuals at high risk for HIV transmission and acquisition meet new sexual partners.([Weir et al., 2003](#_ENREF_97)) The PLACE assessment strategies to be used for this study include community informant and camp verification interviews.

#### 3.2.2.1. Community Informant Interviews

Brief, structured interviews will be conducted with community informants to identify the camps. The goal is to interview as many people as necessary within each ward until there is saturation in the venue lists. The PLACE method recommends interviewing 4 community informants per 1,000 people in catchment area to reach saturation of locations high in HIV risky behaviors. Since camps have already been decided to be the intervention locations, we have estimated that 2 community informants per 1,000 people will be sufficient to develop a saturated list of camps.

Prior to beginning interviews, study staff will inform local government officials as to the purpose and process of the study. Interviewers will then systematically proceed through each *mtaa* (similar to street) in all four wards to complete community informant interviews. Community members familiar with the area and at least 15 years old will be interviewed. Interviewers will approach people encountered in the *mtaa*, and if willing to be interviewed will record they type of community informant for each interview from a pre-developed list (i.e. street vendor, mechanic, security guard, student). Community Informants will then be asked to provide the names of all camps they know of in the area as well as directions to the camp. This phase of data collection is expected to be completed in 2 months.

#### 3.2.2.2 Camp Verification Interviews

Using the list of camps generated during the Community Informant interviews, interviewers will verify the geographical location of camps in the four wards of this study and record camp characteristics using the Camp Verification form. Following directions provided in the Community Informant interviews, research staff will record whether or not they found the camp, refine directions if found, record physical characteristics of the camp, and record GPS coordinates to map and view relative location of camps. The interviewer will then seek a camp leader for the Camp Verification interview, and if not available, other camp members. Camp leaders willing to participate and at least 15 years old will be asked other specific characteristics of the camp such as years of operation, number of members, whether dues are required, activities at the camp, time and day when most busy, and general safety among others. The camp verification component will generate a pool of camps for selection in to the trial. This phase of data collection is expected to be completed in 2 months.

### 3.2.3 Second Primary Aim

To achieve our second primary aim, to evaluate the efficacy of a combined microfinance and health leadership intervention we will conduct a trial among 1252 men in 60 camps that are randomly selected proportionally across four wards. Our primary hypothesis is that the combined microfinance and health leadership intervention will be associated with a lower incidence of sexually transmitted infections and other HIV risk behaviors and less perpetration of violence against female sexual partners over time among men in camps randomized to the intervention as compared to men in camps randomized to the control condition. We also hypothesize that men’s hope for, and orientation towards, the future, as well as the support, social influence and the collective efficacy of their networks, will mediate the effect of the intervention on these outcomes.

## 3.3 Study Duration and Endpoints

The intervention will be implemented for two years, and the total duration of the trial will be 5 years. **The primary endpoints** are sexually transmitted infections including Neisseria gonorrhea (NG), Trichomonas vaginalis (TV), Chlamydia trachomatis (CT), and perpetration of physical or sexual violence against a sexual partner. A random sample of 50% of participating men will be flagged for an STI test at baseline to assess relative prevalence, and all men will be tested at endline. A test of relative prevalence at baseline will aid in establishing equivalency in the two arms; any lack of equivalency then will be controlled for appropriately at endline. All participants will complete a behavioral assessment at baseline, 12 months and 30 months to assess secondary objectives. **Secondary endpoints** are HIV risk and protective behaviors including: gender equity, alcohol and drug use, sexual relations and risk behavior, uptake of HIV counseling and testing; unprotected sexual intercourse; consistent condom use; delay of sexual debut; number of sexual partners, and sexual concurrency. **Key mediators** are hope, future orientation, social cohesion, collective efficacy, emotional distress, sexual networks, social support and social influence.

# 4. STUDY ENROLLMENT

This study will take place in Kinondoni district, the most populous (over 1 million) and most impoverished of the three districts in Dar es Salaam, Tanzania.([Statistics, 2002](#_ENREF_90)) Four wards in Kinondoni characterized by high risk for HIV among young people have been selected for recruitment. These four wards include Manzese (population 66,543), Tandale (population 44,853), Mwananyamala (population 44,344), and Mabibo (population 77,639). In all four wards over a third of the population are males aged 15-29 (range among four wards is 36-38%).([Statistics, 2002](#_ENREF_90)) Illicit drug use, alcohol use, and commercial sex are common to the four wards. In one study of HIV infection among drug users, 66.7% of syringes from male injectors in Manzese and Tandale tested HIV positive and 40% of syringes from male injectors in Mwananyamala tested HIV positive.([McCurdy, Ross, Kilonzo, Leshabari, & Williams, 2006](#_ENREF_55)) Social venues called camps, where young men socialize, have been identified as locations of focus for this study.

## 4.1 Camp Enrollment

### 4.1.1 Definition of Camps

Camps are fixed venues where young men socialize in Dar es Salaam, Tanzania. Camps generally have a democratic system that minimally includes a chairperson, a secretary, and a treasurer. Members often pay dues to belong and maintain written membership records. Camps will serve as the unit of analysis for this trial.

### 4.1.2 Camp Recruitment and Screening

Camps will be identified through the PLACE-based community informant and camp verification interviews. Approximately 2 community informants per 1,000 person population in each of the four participating study wards will be recruited for interviews, or between 400 and 500 individuals. A list of potential camps in the four study wards, and directions to these camps will be developed through Community Informant interviews. All camps identified through Community Informant interviews will then be visited for Camp Verification interviews to confirm existence and current operation, record GPS coordinates, and record characteristics of the camp through interviews with camp leadership. Camps included in the sampling frame will be those confirmed to exist and be in operation, of which GPS coordinates were recorded, and for which at least half of the camp verification interview questions were completed.

### 4.1.3 Camp Eligibility Criteria

Camps must meet a number of requirements to be eligible for selection in to the study. Camps not meeting criteria will be eliminated from the sampling frame. Eligibility criteria include:

- Was not part of the pilot study
- Has 20 members or more
- Has less than 80 members
- Has been in existence at least one year
- Reported no violent incidents during which a weapon was used within the past 6 months
- Research Assistant did not feel unsafe during the verification interview

### 4.1.4 Camp Random Selection

60 camps will be randomly selected in to the study, and later assigned in to one of two conditions – intervention or control. Due to the density of camps within wards and the contiguous nature of some camps, measures will be taken to minimize contamination of potential intervention and control camps before random assignment. The following steps will be taken during the random selection of camps.

1. Local staff will group geographically contiguous camps posing a threat to potential contamination. Eligible camps will be mapped by GPS coordinates on a street layout of the four wards to facilitate grouping. Groups will contain up to 6 camps, individual isolated camps will not need to be put in a group.
2. Groups will be selected for inclusion in the study using probability proportionate to size. Thus, groups with numerous camps of large membership have the potential to be selected more than once.
3. Simple random selection of camp(s) will be completed among camps in each group selected in to the study. Camps from the same group randomly selected in to the study will necessarily receive the same condition during the condition assignment phase.

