## 4.2 Camp Treatment Assignment Procedures

Following random selection, camps will be randomly assigned to a condition 1 or 2, not yet linked to intervention or control. Following up on the grouping procedure used during random selection to minimize potential contamination, groups with single camps selected in the study will first be randomly assigned to condition 1 or 2. Groups with two camps selected in to the study will next be randomly assigned to condition 1 or 2, followed by groups with three camps.

Treatment assignment for the 60 randomly selected and eligible camps will be conducted during a CAB meeting. At the meeting an individual representing condition 1 or 2 will be presented with 5 balloons, each with a folded paper enclosed. In three of the balloons the paper will read “Try again,” one paper will contain the number 1 and one paper will contain the number 2. The individual will be asked to pop one balloon and read the enclosed paper. A “try again” message will prompt the individual to select and pop another balloon. The first number encountered upon popping will represent the group to receive the intervention condition. For example, if the number 2 was encountered first, all camps in Condition 2 are assigned to the intervention condition.

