### 9.1.3 Aim 2 Sampling and Analytical Technique

Aim 2 is to determine whether men in camps randomized to receive a microfinance and health leadership intervention have a lower prevalence of sexually transmitted infections (NG, TV, CT) and report perpetrating less physical or sexual violence against female sexual partners as compared to men in camps not randomized to receive the intervention.

Data gathered from cluster randomized studies such as this one are correlated by common group membership and therefore will be analyzed using methods appropriate to such designs. Since all male camp members in selected camps will be eligible for inclusion (p=1.0), a simple random sample of camps with randomization based upon an equal probability method will be conducted. Sampling weights will be computed as the inverse of probabilities of selection with non-response weights over each wave computed as the inverse of response rates. We will compare odds ratios across group at the 12 month assessment for behavioral outcomes and at 30 months for both behavioral and STI outcomes using SAS SURVEYLOGISTIC version 9.2 to incorporate both the complex nature of sample selection and weighting. Controls for covariates will also be introduced where necessary.

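### Groups of neighbouring camps are sampled and randomised, but the protocol makes the camp the unit of analysis, describes a simple random sample of camps and leaves the group level out of the design effect

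*Protocol*

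**What the plan says.** Section 4.1.4 has local staff put neighbouring camps into groups of up to six; isolated camps stand alone. Selection has two stages: "Groups will be selected for inclusion in the study using probability proportionate to size", and then "Simple random selection of camp(s) will be completed among camps in each group selected in to the study". A group can be drawn more than once, and the consequence is stated outright: "Camps from the same group randomly selected in to the study will necessarily receive the same condition during the condition assignment phase". Section 4.2 carries this into assignment. Groups with one selected camp are assigned first, and the text continues: "Groups with two camps selected in to the study will next be randomly assigned to condition 1 or 2, followed by groups with three camps".

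The statistical text describes something else. Section 4.1.1 says: "Camps will serve as the unit of analysis for this trial". Section 9.1.3 says that "a simple random sample of camps with randomization based upon an equal probability method will be conducted". The same paragraph adds: "Sampling weights will be computed as the inverse of probabilities of selection", together with non-response weights, and plans SAS SURVEYLOGISTIC to account for the selection design and the weighting. It names no cluster variable.

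Section 9.1.1 gives average camp sizes of 36.2 sexually active males and 52 males in all, ICCs of 0.00–0.01 for STI and 0.00–0.032 for behavioural measures, 20% attrition and design effects of 1.4 to 2.3. It mentions no level above the camp.

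**The concern.** Camps that share an arm by design are not independent replicates of that arm. Whatever neighbouring camps have in common beyond what two arbitrary camps share enters the arm difference as group-level variation. A variance estimate that treats each camp as a separate cluster does not see it. Someone programming the analysis from this protocol would find the camp given as the analysis unit and a simple random sample of camps as the design, and could reasonably declare the camp as the cluster. At stake are the width of the confidence intervals and the type I error for both primary endpoints, most of all for violence perpetration, which falls under the higher behavioural ICC. The planned power is also affected, because it counts camps rather than groups.

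**Working it through.** **1. The sections side by side.** Sampling unit: group in 4.1.4, camp in 9.1.3. Sampling method: probability proportional to size and then simple random within group in 4.1.4, simple random in 9.1.3. Unit assigned to a condition: group in 4.1.4 and 4.2. Unit of analysis: camp in 4.1.1. These cannot all describe one design. If any group supplies two or three camps, which 4.2 provides for, there are fewer than 60 independent units.

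**2. The plan's own design effect.** DE = 1 + (m − 1) × ICC, with m = 52 × 0.8 = 41.6 men per camp after 20% attrition.
- ICC 0.01: 1 + 40.6 × 0.01 = 1.41.
- ICC 0.032: 1 + 40.6 × 0.032 = 2.30.

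These are the stated 1.4 and 2.3. The stated sample sizes also follow from camps alone: 54 × 52 = 2808 and 54 × 36.2 = 1954.8. There is no group term in either.

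**3. Adding the group level.** DE_group = 1 + (m − 1)ρ_c + (k̄ − 1)mρ_g. Here ρ_c is the camp ICC, ρ_g is the correlation between men in different camps of one group, and k̄ = Σk²/60 over groups supplying k camps. The factor by which the true SE exceeds a camp-clustered SE is √(DE_group/DE_camp). True alpha is 2(1 − Φ(1.96/factor)).

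The protocol states neither the mix of group sizes nor ρ_g. Two mixes of 60 camps are assumed:
- 44 singles, 5 pairs, 2 triples: 51 groups, k̄ = (44 + 20 + 18)/60 = 1.37.
- 30 singles, 9 pairs, 4 triples: 43 groups, k̄ = (30 + 36 + 36)/60 = 1.70.

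ρ_g is taken from half of ρ_c to all of it. Worked line: m = 41.6, ρ_c = 0.032, 43 groups, ρ_g = 0.016 gives 2.30 + 0.70 × 41.6 × 0.016 = 2.77 and √(2.77/2.30) = 1.10.

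| m | ρ_c | Groups | DE camp | DE group | SE factor | True alpha |
|---|---|---|---|---|---|---|
| 41.6 | 0.032 | 51 | 2.30 | 2.54–2.79 | 1.05–1.10 | 0.062–0.075 |
| 41.6 | 0.032 | 43 | 2.30 | 2.77–3.23 | 1.10–1.19 | 0.074–0.098 |
| 41.6 | 0.01 | 51 | 1.41 | 1.48–1.56 | 1.03–1.05 | – |
| 41.6 | 0.01 | 43 | 1.41 | 1.55–1.70 | 1.05–1.10 | – |
| 20.8 | 0.032 | 43 | 1.63 | 1.87–2.10 | 1.07–1.13 | 0.067–0.084 |

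The last row uses the study size in the Protocol Summary, 1249/60 = 20.8 men per camp. Limits at m = 41.6 and ρ_c = 0.032: with all groups single or ρ_g = 0 the factor is 1.00; with all triples and ρ_g = ρ_c, DE is 4.96, the factor 1.47 and alpha 0.18.

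**4. Power.** Section 9.1.1 states no control rate, so its detectable OR of 0.65 for violence cannot be checked exactly. At DE 2.30 with 20% attrition it corresponds to a rate of about 26–27%. Using the only violence rate in the protocol, the lifetime 41% of Section 1.7, with N = 2808, power at OR 0.65 is 0.90 at DE 2.30, 0.83–0.87 with 51 groups and 0.78–0.84 with 43 groups. The OR detectable with 80% power moves from 0.69 to 0.66–0.68 and 0.64–0.66 respectively.

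**The case against.** The strongest reply is that Section 9.1.3 names no cluster variable. It promises methods suited to cluster-randomised data, weights from the selection probabilities and a design-based procedure. The first-stage unit is the natural cluster in such a procedure, and if the group is declared the standard errors are valid. CLUSTER statements and degrees of freedom are commonly left to the SAP, which is not at hand. This stands as far as it goes: a reader might infer that the standard errors will be too small, and the protocol does not establish that. The reply does not remove the point. The protocol states the sampling design wrongly and fixes the analysis unit one level too low, and a design-based procedure is only as right as the design declared to it.

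Other inferences also go further than the text.
- **Weights.** A reader might conclude that the weights will be wrong. They are already defined as inverse selection probabilities, and the equal-probability phrase can be read as describing the randomisation. If size in 4.1.4 means number of camps and each draw takes one camp, selection is equal-probability. If it means membership, as the remark about large membership suggests, it is not.
- **Number of units.** A particular count such as 40 or 30 would be an assumption, not a result.
- **Strata.** Leaving out the group-size classes used in assignment generally makes standard errors conservative, not too small.
- **Degrees of freedom.** The effect is minor: the critical t value is 2.00 on 58 df and 2.05 on 28 df.
- **Mixing of members.** The protocol groups camps for geographic closeness and possible contamination. It does not say that their members mix, and the eligibility questions in Appendix D deal with membership of two study camps. Positive correlation is plausible but not documented.

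**Conclusion.** The contradiction is real and sits in the protocol's own text: groups are sampled and randomised, while the analysis unit, the description of sampling and the design effect are all set at camp level. Understated standard errors follow only if three conditions hold together: the camp is the declared cluster, some groups supply two or three camps, and camps in a group are positively correlated.

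Under the assumed 43 to 51 groups and a group-level ICC of half to all of the camp ICC, at 41.6 men per camp, the true SE is about 5–19% larger than reported for behavioural outcomes at ICC 0.032 (true alpha about 0.06–0.10). It is about 3–10% larger for STI at ICC 0.01. At 20.8 men per camp, ICC 0.032 and 43 groups it is about 7–13% larger. Both ICCs are the top of their stated ranges, so smaller effects, down to none, are possible. If the group is declared as the cluster, the inference is sound, and what remains is that the stated power omits the group level.

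**What to change.** - **Sections 4.1.1 and 9.1.3:** name the group of neighbouring camps (an isolated camp being its own group) as the unit of randomisation and as the SURVEYLOGISTIC cluster, with degrees of freedom based on the number of groups.
- **Section 9.1.3:** replace the sentence on a simple random sample of camps with the actual design, groups drawn with probability proportional to size and then camps drawn at random within groups. Compute the planned selection weights from those two-stage probabilities.
- **Section 9.1.1:** restate the design effect and detectable effects with a group-level term and the actual number of groups, giving the group-level ICC assumed.

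The cost is a change of wording, slightly wider intervals and a somewhat less favourable stated detectable effect. If groups add no correlation, little is lost. Running the primary comparison without selection weights, or declaring the one-, two- and three-camp classes as strata, is optional and not part of this correction; the number of three-camp groups is unknown and may be too small to form a stratum.
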